#### 2.8.3 Secondary outcomes

1) Changes in hepatic steatosis factors by ultrasound grading of steatosis.2) Changes in metabolic parameters: glycated hemoglobin (HbA1c) levels, fasting plasma glucose (FPG), 2-h plasma glucose (2h-PG), fasting insulin, blood lipids including total cholesterol (TC), triglycerides (TG), high-density lipoprotein-cholesterol (c-HDL), low-density lipoprotein (c-LDL), apolipoprotein A (ApoA), and apolipoprotein B (ApoB).3) Changes in anthropometric parameters: Waist-to-height ratio (WHtR), Body Mass Index (BMI), waist circumference (WC), hip circumference (HC).4) Changes in hepatic fibrosis factors and hepatic function: The changes in Fibrosis 4 Score (FIB-4, http://gihep.com/calculators/hepatology/fibrosis-4-score/) can be calculated by the formula:

$$\mathrm{Age}\;\left(\mathrm{years}\right)\text{x}\;\mathrm{AST}\;/\mathrm{PLT}\;\left(\times 10^{9}/L\right)\text{x}\sqrt{\mathrm{ALT}}$$

The units of measurement for ALT and AST are aligned with those for age and PLT.

Definitions for the following abbreviations: AST: Aspartate aminotransferase; PLT: platelet; ALT: Alanine aminotransferase.5) Changes in visceral fat area.

All measurements will be performed at baseline and at week 12. Additional FPG and blood lipid test will be performed at week 6.

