### 2.4 Inclusion criteria

1) All participants must meet the individual diagnostic criteria for T2DM and NAFD. The diagnostic criteria for T2DM (American Diabetes Association Professional Practice Committee, 2022) includes:• Fasting plasma glucose (FPG) ≥126 mg/dl (7.0 mmol/L) or 2-h plasma glucose (2-h PG) ≥200 mg/dl (11.1 mmol/L) during an oral glucose tolerance test or HbA1c ≥ 6.5% (48 mmol/mol).• Typical symptoms of hyperglycemia (excessive thirst, polyuria, weight loss, hunger, pruritus, or coma) or hyperglycemic crisis plus a random plasma glucose (PG) ≥200 mg/dl (11.1 mmol/L). Patients without typical symptoms of diabetes need to be re-examined for confirmation. Fasting state: no intake of calories for at least 8 h; random plasma glucose: blood glucose at any time of day, regardless of the last meal time (cannot be used to diagnose abnormal fasting blood glucose or abnormal glucose tolerance). The diagnostic criteria for NAFLD (European Association for the Study of the Liver (EASL) et al., 2016) (Chalasani et al., 2018) requires:• Evidence of excess liver fat accumulation (hepatic steatosis) on ultrasound imaging.• Exclusion of excessive daily alcohol consumption ≥30 g for men and >20 g for women (Ratziu et al., 2010).• Acute or chronic viral hepatitis (e.g., hepatitis C), autoimmune hepatitis, hemochromatosis, Wilson’s disease, alcoholic liver disease, drug-induced liver disease, liver cirrhosis, inborn errors of metabolism (e.g., cholesterol ester storage disease), or other causes of chronic liver disease.2) All participants must meet the diagnostic criteria for heat stagnation syndrome in the liver and stomach in accordance with the Guidelines for Clinical Research of Chinese Medicine (Zheng, 2002) outlined below.• Any two main symptoms including dry mouth, bitter and sticky mouth, heaviness in the head and body, and/or obesity• Any two secondary symptoms including fullness and distention of the chest or abdomen, upset or irritable demeanor, rapid digestion of food and polyorexia, deep-colored or turbid urine, and/or unpleasant or constipated stools.• Tongue condition: red tongue, yellow fur.• Pulse condition: stringy and rapid pulse or slippery and rapid pulse.3) Participants should be between the ages of 20 and 75 years.4) The experimental group should not have taken traditional Chinese medicine for diabetes and NAFD orally for at least 2 weeks before enrollment.

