### 2.10 Sample size calculation

In a previous study (Xu, 2017), JTTF reduced HbA1c levels in diabetic patients with heat stagnation in liver and stomach after 12 weeks of treatment (treatment group: 6.94±0.88%, control group: 7.64±0.72%, mean difference between the two groups: 0.7%). Considering a type I error of 5% (α = 0.05) and a power of 85%, the experimental and control groups were allocated at a ratio of 1:1. The sample size was calculated using Power Analysis and Sample Size (PASS) software (version 15.0); a total of 76 patients will be required. According to the dropout rate of 20%, we set the final sample size to 96, with 48 patients in each group, considering the number of dropout samples.

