## 3 Statistical methods

### 3.1 Data analysis

Data will be analyzed using SPSS software (Version 24.0; IBM Corp. Armonk, NY, United States). Continuous variables will be represented as means, standard deviations, medians, and minimum/maximum values. If the data confirms normal distribution, an independent sample *t*-test will be used to assess the differences between the two groups, and a paired sample *t*-test to compare the differences between groups before and after the intervention. Wilcoxon signed-rank test will be used for data that does not conform to normal distribution. Grade data will be analyzed using Wilcoxon’s signed-rank test or the CMHχ2 test. Statistical significance will be set at *p* < 0.05.

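### FIB-4 change is most naturally read as an unadjusted raw change, which weights patients by age and baseline level; baseline-adjusted ANCOVA on a prespecified scale is an optional improvement

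*Protocol article*

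**What the plan says.** Protocol article, section 2.8.3, lists "Changes in hepatic fibrosis factors and hepatic function: The changes in Fibrosis 4 Score" and says that the score "can be calculated by the formula" printed there, in which age multiplies a function of AST, platelets and the square root of ALT. On timing it says "All measurements will be performed at baseline and at week 12". It does not say whether the change is an absolute difference, a percentage or a log ratio.

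Section 3.1 covers all continuous variables together: "If the data confirms normal distribution, an independent sample" t-test "will be used to assess the differences between the two groups". For the other case, "Wilcoxon signed-rank test will be used for data that does not conform to normal distribution". It mentions neither a transformation nor adjustment for baseline.

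Section 2.4 sets the age range: "Participants should be between the ages of 20 and 75 years".

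Section 2.10 sizes the trial on HbA1c (76 evaluable patients, 96 with dropout). No SD, effect or power is given for FIB-4.

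**The concern.** FIB-4 is a product of age and a laboratory term. Age cannot respond to treatment, but it multiplies every patient's raw change, and so does the baseline laboratory level when changes are proportional. A t-test on raw change then gives unequal weight to equal proportional responses. It also ignores the baseline score, which the trial collects anyway.

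FIB-4 is the only fibrosis score among the secondary outcomes, and inhibiting liver fibrosis is part of the hypothesis in section 2.1.1. What is at stake is precision on that outcome. Nothing here biases the comparison between randomised arms.

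**Working it through.** **Plan's own figure.** There is none for FIB-4, so every SD and effect below is an assumption.

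**Step 1: algebra.** Write FIB-4 = Age × g, where g is the laboratory term. With age held at baseline:

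- raw change = Age × (g₁ − g₀) = baseline FIB-4 × (g₁/g₀ − 1);
- log change = log(g₁/g₀), from which age cancels.

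This holds whether √ALT is read in the numerator or the denominator of the printed formula. At the eligibility limits, the same change in g counts 75/20 = 3.75 times as much in the oldest as in the youngest patient.

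**Step 2: closed form, proportional changes only.** If g₁/g₀ is independent of baseline, the efficiency of the raw analysis relative to the proportional one is about 1/(1 + CV²), where CV is that of baseline FIB-4.

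- Age alone, assumed uniform on 20 to 75: CV = (55/√12)/47.5 = 0.334, and efficiency = 1/(1 + 0.334²) = 0.90.
- Total CV assumed 0.5: efficiency = 1/1.25 = 0.80, as if 48 × 0.80 ≈ 38 patients per arm were analysed.

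**Step 3: who carries the weight.** In simulations with proportional noise, the oldest third supplied 48–59% of the squared raw change and the highest-baseline third 55–78%, against 33% under equal weight.

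**Step 4: power over a grid.** Two-sided 5%, 4000 trials per setting, 38 per arm, log-SD of within-patient change 0.2, effect set so that the log test has about 80% power. Ages are normal (52, SD 11, clipped to 20–75) or uniform on 20–75. In the additive model the noise SD is 20% of mean baseline.

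| Age | Log-SD of baseline g | Proportional: raw t | Proportional: rank-sum on raw | Proportional: log t | Additive: raw t | Additive: log t |
|---|---|---|---|---|---|---|
| normal | 0.20 | 74.5% | 74.6% | 79.0% | 79.0% | 68.7% |
| normal | 0.35 | 70.3% | 72.5% | 78.5% | 79.7% | 63.3% |
| normal | 0.50 | 66.2% | 71.9% | 79.4% | 78.6% | 57.8% |
| uniform | 0.20 | 72.8% | 73.6% | 80.5% | 78.5% | 63.1% |
| uniform | 0.35 | 68.5% | 71.8% | 78.9% | 78.7% | 59.0% |
| uniform | 0.50 | 64.7% | 70.2% | 78.2% | 78.1% | 55.9% |

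Over the full grid (38 and 48 per arm, change log-SD 0.2 to 0.3) the log scale gains about 4–17 points under the proportional model and loses about 10–23 under the additive one.

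**Step 5: power from the laboratory components.** Assumed baseline log-SDs: AST 0.35, ALT 0.45 (correlation 0.7), platelets 0.25. Assumed change log-SDs: 0.22, 0.28 (correlation 0.7), 0.12. Effect: a fall of 0.12 in log FIB-4, 1 − exp(−0.12) ≈ 11%. The section 3.1 rule was run as a t-test unless either arm fails a Shapiro test, then a rank-sum test.

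| Per arm | Age | Raw t | Section 3.1 rule | Log t | Log − raw | Log − rule |
|---|---|---|---|---|---|---|
| 48 | uniform 20–75 | 74% | 78% | 83% | 9 | 5 |
| 48 | normal (50, SD 11) | 77% | 79% | 84% | 7 | 5 |
| 38 | uniform 20–75 | 64% | 67% | 75% | 11 | 8 |
| 38 | normal (50, SD 11) | 66% | 68% | 74% | 8 | 6 |

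Across repeat runs the gain was about 7–13 points over the raw t-test and about 5–9 over the rule. With additive changes, the log scale lost about 6–16 points.

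**Step 6: baseline adjustment.** Adjusting the raw-scale comparison for baseline gained about 5–7 points when the proportional model included baseline measurement noise. It cost no more than about 2 points in any setting.

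**The case against.** The strongest objection is that the raw scale is inferred. Section 2.8.3 speaks only of changes, section 3.1 is a generic paragraph, and the scale of one secondary outcome is commonly left to an analysis plan, which is not shown. That stands as a limit on certainty: the plan may already specify a transformation. But the article does name the outcome and the test, and the test it names is unadjusted.

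Four stronger readings are tempting, and none is supported.

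- *Older patients dominate the result.* They carry extra weight, but the 3.75 ratio compares the two eligibility limits, age alone costs about 10% efficiency even with uniform ages, and baseline spread matters more.
- *Power is lost.* This is true only if changes are roughly proportional. Under additive changes the raw scale has more power, and the documents contain no FIB-4 data to choose between the models.
- *A log analysis costs nothing.* It needs no extra patients or data, but it changes the estimand from a mean difference to a ratio of geometric means and can lose power.
- *Birthdays between visits distort the score.* A birthday shifts FIB-4 by 1/75 = 1.3% to 1/20 = 5%, in about 12/52 = 23% of patients, and randomisation balances it. The effect is negligible.

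It is also fair to say that section 3.1 already sends skewed changes to a rank test, which recovers part of the gap. This credit assumes a rank-sum test. The signed-rank test named there is a paired test, which is a separate matter.

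**Conclusion.** The point holds as an optional improvement, not as an error or contradiction. Two parts are firm: a raw FIB-4 change is scaled by age, and the stated test does not use the baseline score. The weighting by baseline level and the benefit of a log scale are conditional: a gain of about 7–13 power points over the raw t-test (about 5–9 over the section 3.1 rule read as rank-sum) if changes are proportional, and a loss of about 6–16 points if they are additive, both at 38 to 48 per arm. These figures rest on assumed laboratory SDs, effects and age distributions, and on reading the planned change as raw. Baseline adjustment does not depend on the choice of scale; it helps where the baseline is measured with noise and costs little otherwise. FIB-4 is an unpowered secondary outcome, so the trial's main conclusions are not affected.

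**What to change.** In sections 2.8.3 and 3.1, state that week-12 FIB-4 will be compared between arms by ANCOVA adjusted for baseline FIB-4, with age at baseline used in both scores. If proportional change is judged plausible, prespecify log FIB-4 as the analysis scale for both the outcome and the baseline covariate, and report the ratio of geometric means with its 95% CI. Report the raw-scale baseline-adjusted difference as a sensitivity analysis. Fix the scale before unblinded data are seen.

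The cost is a sentence or two of analysis wording and no new data. The downsides are that the effect is expressed as a ratio instead of score points and that power may fall if changes are in fact additive.

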## 2 Methods and analysis

### 2.1 Study objectives

#### 2.1.1 Primary objective

The primary objective of this clinical trial is to assess the efficacy and safety of JTTF for the treatment of T2DM combined with NAFLD. We hypothesized that JTTF combined with conventional Western medicine would be more effective than the single use of conventional Western medicine alone in reducing fat accumulation, inhibiting liver fibrosis, regulating blood lipids, lowering blood glucose levels, and alleviating the clinical symptoms of patients with T2DM and NAFLD.

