### 2.5 Exclusion criteria

1) Patients with liver or kidney dysfunction: aspartate transaminase [AST] or alanine transaminase [ALT] >2.5 times the normal upper limit or creatinine >115 μmol/L.2) Patients with chronic diseases, such as hypertension, cardiovascular, cerebrovascular, autoimmune diseases, chronic kidney diseases and psychiatric diseases who cannot follow research procedures.3) Patients who are using insulin.4) Allergic constitution or a history of drug allergies.5) Pregnant and lactating women.6) Patients who participated in other clinical studies within the preceding three months.

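### The FIB-4 formula in section 2.8.3 has no bracket joining platelets and √ALT, so coded as printed it multiplies by √ALT instead of dividing by it

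*Protocol article*

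**What the plan says.** Section 2.8.3 of the protocol article lists the change in FIB-4 as a secondary outcome. It gives a calculator link and, in the same sentence, says the score "can be calculated by the formula" that follows. The formula is set on one line: age in years, times AST, a slash, PLT in units of 10⁹/L, times the square root of ALT. The only brackets enclose units.

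The next sentence reads "The units of measurement for ALT and AST are aligned with those for age and PLT". No unit for either enzyme is given, and there is no worked value or cut-off that would show the intended grouping.

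On timing, the section states "All measurements will be performed at baseline and at week 12", and Table 1 agrees for FIB-4. The hypothesis in section 2.1.1 includes "inhibiting liver fibrosis". FIB-4 is the only fibrosis measure named among the outcomes.

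**The concern.** This line is the only derivation rule the article gives for FIB-4. Section 3.1 names SPSS as the analysis software. Typed there as printed, the expression is evaluated from left to right, so √ALT lands in the numerator.

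The discrepancy between the two readings is not a fixed scale factor that would cancel between arms. It is each patient's own ALT at that visit, and treatment may change ALT. The Introduction cites earlier work in this population reporting an effect of the formula on liver function. Section 2.5 excludes patients only when AST or ALT is ">2.5 times the normal upper limit", so raised values with room to fall can enter the trial. In the printed form a fall in ALT, by itself, lowers the score. In the bracketed form the same fall raises it. Coding the wrong form could therefore change what the trial reports about fibrosis.

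The units sentence does not help. Enzyme activity cannot share a unit with years or with a platelet count.

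**Working it through.** The article states no FIB-4 value, so there is no figure to reproduce. The formula comes from section 2.8.3. All patient values below are assumptions for illustration.

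**1. The two readings**

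- As printed, usual precedence: W = (Age × AST / PLT) × √ALT
- Bracketed: B = (Age × AST) / (PLT × √ALT)
- Ratio: W / B = √ALT × √ALT = ALT, whatever the age, AST and PLT

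**2. Size of the discrepancy**

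| Age | AST | PLT | ALT | W (as printed) | B (bracketed) | W / B |
|---|---|---|---|---|---|---|
| 50 | 25 | 220 | 20 | 25.4 | 1.27 | 20 |
| 50 | 40 | 200 | 40 | 63.2 | 1.58 | 40 |
| 50 | 40 | 220 | 60 | 70.4 | 1.17 | 60 |
| 55 | 80 | 200 | 100 | 220 | 2.20 | 100 |

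Second row in full: 50 × 40 / 200 = 10 and √40 = 6.325, so W = 10 × 6.325 = 63.2 and B = 10 / 6.325 = 1.58.

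**3. Direction of change**

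Hold age and PLT fixed. Let AST fall by a proportion a and ALT by a proportion b.

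- W is multiplied by (1 − a) × √(1 − b), which is below 1 whenever either enzyme falls and neither rises.
- B is multiplied by (1 − a) / √(1 − b), which is above 1 when a < 1 − √(1 − b).

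So W falls while B rises exactly when the AST fall is below this limit:

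| ALT fall | Forms move in opposite directions if AST falls by less than |
|---|---|
| 10% | 5.1% |
| 20% | 10.6% |
| 30% | 16.3% |
| 40% | 22.5% |
| 50% | 29.3% |

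**4. Assumed single-patient changes**

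| Age, PLT | AST | ALT | W | B |
|---|---|---|---|---|
| 50, 200 | 40 to 35 | 40 to 30 | 63.2 to 47.9 (−24%) | 1.58 to 1.60 (+1%) |
| 50, 200 | 40 to 38 | 40 to 30 | −18% | +10% |
| 50, 220 | 40 to 36 | 60 to 40 | 70.4 to 51.8 | 1.17 to 1.29 |
| 50, 220 | 40 to 30 | 60 to 40 | 70.4 to 43.1 | 1.17 to 1.08 |

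In the first row a = 12.5%, just inside the limit of 1 − √0.75 = 13.4%, so B barely rises. In the last row a = 25% exceeds the limit of 1 − √(40/60) = 18.4%, so both forms fall.

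**The case against.** The best defence is that nobody will code this line literally. The sentence names an established score and links a calculator, and its wording is permissive. Writing everything after the slash as the denominator is common loose notation. The derivation program would sit in a fuller document that is not shown. Most of this stands: a notation slip is the likeliest explanation, and anyone using the calculator would not meet the problem. It does not remove the point, because the article still prints a rule that, followed as written, gives something other than the bracketed score.

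A reader might infer three stronger things that the documents do not support.

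- **That the trial's values will be ALT-fold too large.** The article nowhere prints the grouping it intends, and the linked page cannot be consulted here. What can be shown is that the two readings differ ALT-fold.
- **That a treatment effect on fibrosis would be reversed.** Opposite movement occurs for some AST and ALT patterns and not for others. The examples are single patients with assumed values, and the article gives no size for any expected change in liver enzymes.
- **That any fall in ALT would look like a large fall in the score.** As printed, the score varies with √ALT. A 10% fall in ALT with AST unchanged lowers it by about 5% (1 − √0.9), and a rise in AST can cancel that.

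The units sentence may simply be awkward wording for consistent units. It has no bearing on the grouping.

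**Conclusion.** The point holds as a defect in a printed derivation rule. Without a bracket, the formula read literally differs from the bracketed form by a factor equal to each patient's ALT (20 to 100 in the assumed cases) and depends on ALT in the opposite direction. Whether the two forms change in opposite directions depends on the limit 1 − √(1 − ALT fall), with age and PLT fixed and both enzymes falling.

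Harm follows only if the line is coded as written, and describing the result as a mis-scoring assumes that the bracketed form is the intended one. The linked calculator can confirm that.

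The reach is limited. Section 2.8.2 makes visceral fat area and the TCM score the primary outcomes, and the sample size in section 2.10 rests on HbA1c, so neither is affected. A reader might take the mention of fibrosis in section 2.1.1 to mean that a primary result is at risk; FIB-4 is a secondary outcome. It is nevertheless the only fibrosis measure that could inform that part of the hypothesis, so the correction should be made before analysis.

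**What to change.** Print and program the score as (Age × AST) / (PLT × √ALT), with both pairs of brackets. Before any data are analysed, run a few test patients through the derivation program and through the calculator cited in the same sentence, and confirm that they agree. Include patients whose ALT differs widely, since the discrepancy scales with ALT.

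Replace the units sentence with the units actually used: age in years, AST and ALT in the laboratory's reporting unit, and PLT in 10⁹/L.

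The cost is a corrected formula and units sentence in the protocol, a check of the derivation code and a few test cases. Nothing changes in conduct, visits or sample size.

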#### 2.8.4 Monitoring outcomes

Homeostasis model assessment for insulin resistance (HOMA-IR) and homeostatic model assessment for β-cell function (HOMA-β) will be performed at baseline and at week 12.

#### 2.8.5 Biological specimen analysis outcomes

Untargeted and targeted metabolomics tests will be performed sequentially on fasting blood and urine samples collected at enrollment and at the end of the 3-month treatment period. Biological samples will be centrifuged and stored in a -80°C refrigerator. Assays will be performed using liquid chromatography-mass spectrometry (LC-MS) techniques for microscopic high-throughput measurements. Through basic analysis, multivariate statistical analysis, and difference analysis, the differential metabolites in serum and urine, before and after treatment, will be compared between the two groups. Further targeted metabolomic analyses will be performed to categorize differential metabolites screened by untargeted metabolomics, as well as explore their possible metabolic pathways. The exploratory results will be combined with clinical efficacy evaluation to determine the mechanism of action of JTTF in the treatment of T2DM complicated with NAFLD from the perspective of metabolomics and small-molecule compounds.

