The main components of JTTF have been analyzed by High Performance Liquid Chromatography (HPLC) in our previous study (Zhang Q. et al., 2021), which can be seen in Supplementary Material S1. On the basis of reference standard data, chromatographic elution behavior, chemical composition data, mass fragmentation pattern and HPLC results, the chemical components of JTTF were identified as chlorogenic acid, anthocyanin-7-glucoside, tannic acid B, aloe rhodopsin and haragoside. By means of the validation of network pharmacology and in vitro experiments, it proves that JTTF plays an important role in promoting insulin secretion and regulating glucolipid metabolism by acting on the PI3K-Akt pathway, an important pathway for insulin signaling and glucose regulation (Zhang Q. et al., 2021). Related research has demonstrated that JTTF can inhibit the expression of inflammatory factors associated with endoplasmic reticulum stress, thereby alleviating this condition (Jiang et al., 2018), improving IR, and increasing insulin sensitivity (Liu et al., 2021). At the same time, it can activate the IRE1α/JNK pathway, which is closely related to IR and pancreatic β-cell apoptosis to reduce the apoptosis of pancreatic islet cells and prevent and treat T2DM (Piao et al., 2018). Studies showed that blood glucose and lipid levels, as well as IR levels of diabetic ZDF rats were significantly improved by high-dose JTTF (Liu et al., 2021). Related clinical studies have shown that JTTF may reduce glycated hemoglobin, blood glucose, and inflammatory factor levels, regulate lipid and insulin resistance levels in T2DM patients (Jin et al., 2020), and have significant efficacy in reducing liver function, BMI, waist circumference, and TCM symptom scores in T2DM combined with NAFLD patients (Gong, 2017).

Herein we investigate the clinical efficacy and safety of JTTF for the treatment of T2DM combined with NAFLD. It is necessary to design and conduct this trial study as the mechanism of action of this formula has not been explored at the molecular level.

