#### 2.1.2 Secondary objective

The secondary objective of this study was to identify differential metabolites in the serum and urine of patients before and after JTTF treatment to determine possible relevant metabolic pathways and routes of action in T2DM combined with NAFLD. Furthermore, we explored the regulatory effects and mechanisms of JTTF action on various aspects including lipid and glucose regulation at the metabolic level.

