### 2.2 Study design

This study is designed as a 12-weeks, single-center, double-armed, parallel, randomized, controlled clinical trial. A total of 96 eligible participants will be recruited from Shenzhen Hospital of Guangzhou University of Chinese Medicine (Futian) and randomized in a 1:1 ratio into two groups to receive basic treatment. As a supplement to the clinical study, participants’ fasting serum and urine samples will be subjected to untargeted and targeted metabolomic assays. Liquid chromatography–mass spectrometry (LC-MS) will be used to compare metabolites before and after treatment in the experimental and control groups. Basic analysis of metabolites, multivariate statistical analysis, pathway enrichment analysis, and topological analysis of the screened differential metabolites will be performed.

All patients should have voluntarily participated and signed an informed consent form with good compliance. Informed consent will be obtained from all participants prior to enrollment. A flowchart and schedule of the clinical trial is shown in Figure 1 and Table 1, respectively. The protocol was designed according to the Standard Protocol Items: Recommendations for Interventional Trials (SPIRIT) guidelines (Chan et al., 2013) and the Declaration of Helsinki. The SPIRIT checklist is shown in Supplementary Material S2.

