### 2.7 Intervention

The control group will receive conventional basic treatment, including health education and oral medications to stabilize blood sugar, blood pressure, and lipid levels. Meanwhile, the experimental group will be given JTTF on the top of the control group. In this study, Chinese herbal medicine concentrated granules (CCMG) will be used to replicate the traditional method of preparing herbal tonics by using herbs as raw materials and modern extraction and concentration techniques. All herbal pellets will be manufactured and supplied by China Resources Sanjiu Pharmaceutical Co. and also tested by their quality management department for compliance with the grade standards of the Chinese Pharmacopoeia (2020 edition). Voucher specimens of all drugs are deposited at the Bureau of Traditional Chinese Medicine, Shenzhen Hospital, Guangzhou University of Chinese Medicine (Futian) (Shenzhen, China). The decoction and packing of botanical drugs are uniformly operated by Kangmei Pharmaceutical Co., Ltd. Smart Pharmacy. CCMG is based on the “Research Guidelines for Single Flavor Chinese Medicine Concentrated Granules” and the “Pharmacopoeia of the People’s Republic of China” (2010 edition). Extracted in a fully enclosed pipeline production line in GMP workshop. All herbs are mixed in the proportions described above, steeped in 10 volumes of pure water for 0.5 h, heated to boiling, decocted for 1 h. The water extract is filtered and the residue is then decocted with 8 volumes of pure water for 40 min. The two liquid extracts are combined, settled and filtered, concentrated to a thick paste, and processed into concentrated granules by spray drying. The process parameters are screened by orthogonal design method according to the composition characteristics of different species. A certain amount of soluble dextrin is added as an auxiliary material to assist the molding. The dry extract ratios of the five raw herbs were 1:6 for *Coptis chinensis*, 1:2.4 for *Rheum palmatum*, 1:10 for *Astragalus mongholicus*, 1:6.7 for *Salvia miltiorrhiza* and 1:6 for *Bupleurum chinense*. The final JTTF is made by combining the individual herbal pellets in the leaching ratio, which is equivalent to 64 g of raw herbs. It is packaged with aluminum-plastic-aluminum composite film (BOPP/AL/CPE) packaging material sealed on four sides. Dissolve the concentrated granules in 200 ml of boiling water and take warm. Take twice daily, half an hour after breakfast and dinner. The observation period will be administered for three months.

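### Metabolomic samples are taken at baseline and at the end of JTTF dosing in one arm only, so JTTF's own compounds may be selected as differential metabolites and read as mechanism.

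*Protocol article*

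**What the plan says.** The secondary objective (section 2.1.2) is to find serum and urine metabolites that differ before and after JTTF, "to determine possible relevant metabolic pathways and routes of action in T2DM combined with NAFLD". Section 2.2 states that participants' "fasting serum and urine samples will be subjected to untargeted and targeted metabolomic assays". Section 2.8.5 gives the sampling times as "collected at enrollment and at the end of the 3-month treatment period", and Table 1 ticks both sample types at baseline and at Visit 4 (12 weeks ± 7 days) only.

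On exposure, section 2.7 gives JTTF to the experimental arm alone, on top of the treatment that the control arm receives. Its instructions are "Take twice daily, half an hour after breakfast and dinner" and "The observation period will be administered for three months". No drug-free interval before the final sample is stated. Section 2.9 describes the trial as open-label.

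On analysis, section 2.8.5 sets out an untargeted LC-MS screen and a difference analysis in which "the differential metabolites in serum and urine, before and after treatment, will be compared between the two groups". A targeted assay then categorizes the hits. Section 2.2 adds pathway enrichment and topological analysis. The declared end point of this sequence is JTTF's mechanism of action.

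The Introduction reports that the team has already profiled the product: "the chemical components of JTTF were identified as chlorogenic acid, anthocyanin-7-glucoside, tannic acid B, aloe rhodopsin and haragoside". The profile is in Supplementary Material S1.

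**The concern.** An untargeted LC-MS screen registers small molecules whatever their origin. A constituent of the herbs, or something the body makes from it, can be present in the JTTF arm at week 12 and scarce or absent elsewhere. Such a compound is a marker that the patient took the product. It is not evidence of what the product did to glucose or lipid metabolism. Yet it shows exactly the pattern that the stated comparison looks for.

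At stake is the secondary objective. If exposure markers are among the hits, they take up targeted assays, enter the enrichment and topology analysis, and can be reported as part of the mechanism. Correction for multiple testing does not protect against this, because the differences are real. Only their interpretation would be wrong.

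**Working it through.** The plan gives no figure to reproduce on this point. The check is therefore a reading of the design, followed by an illustration under assumptions.

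**1. Does either contrast cancel JTTF exposure?** From sections 2.7 and 2.8.5 and Table 1:

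| | Baseline | Week 12 |
|---|---|---|
| JTTF arm | before JTTF | end of twice-daily JTTF |
| Control arm | no trial JTTF | no trial JTTF |

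- Before/after within the JTTF arm: exposure changes.
- Between arms at week 12: exposure differs.
- Difference of the two changes: exposure changes in one arm only.

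All three carry the exposure difference, so none removes herb-derived features.

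**2. Does a later stated step remove them?** The order is untargeted screen, difference analysis, targeted assay, then pathway and topology analysis, then mechanism. The targeted step takes in what the screen selected. The text gives no rule that sorts herb-derived from endogenous compounds at any stage.

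**3. Does fasting remove them?** Samples are fasting. The article defines fasting as "no intake of calories for at least 8 h", but only for the diagnosis of diabetes. If that definition also applied to the samples, a dose after dinner would precede a morning sample by about 8 h or more. This may lower carry-over. It does not show that carry-over is absent, and the time of the last dose is not given.

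**4. How strongly could such a feature stand out?** This is an illustration, not a prediction. Assumptions: 38 evaluable patients per arm (76/2, from the 76 in section 2.10), 0 of 38 control samples positive, and k of 38 JTTF samples positive. The values of k are assumed; the documents give no detection rates. With equal arms and a zero cell, the two-sided Fisher p is 2 × C(38,k)/C(76,k):

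| k of 38 | p |
|---|---|
| 10 | 9.9e-4 |
| 20 | 6.2e-8 |
| 30 | 7.6e-14 |
| 36 | 2.3e-19 |

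Under a Bonferroni limit at 0.05, the feature at k = 10 would survive a screen of up to about 50 features (0.05/9.9e-4). At k = 20 it would survive about 800,000 (0.05/6.2e-8). A commonly detected constituent would rank near the top of the list. A sparsely detected one might not be selected at all.

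**The case against.** The strongest objection is that this is silence in a condensed article. Feature annotation and the handling of foreign compounds are commonly left to a fuller plan, which is not shown. The article describes no feature filter of any kind, calls the metabolomic results exploratory, and has a categorizing step at which a chemist could recognize herbal compounds. The team already holds the product's profile. This stands in part: the article cannot be read as saying that herbal compounds will be kept. But the sampling times, the one-arm exposure, the sequence of analyses and the mechanism inference are all stated. Carried out as written, that sequence can select exposure markers. The point therefore rests on what the article fixes as well as on what it leaves out.

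Stronger readings are tempting, and the documents do not support them:

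- *JTTF compounds will appear and will be read as mechanism.* This depends on pharmacokinetics, last-dose timing and annotation, none of which is given. The samples are fasting and are taken at the end of treatment, so even active dosing on the sampling day is an inference. The supported word is may.
- *Background glucose, lipid and blood pressure drugs raise the same problem.* Section 2.7 gives conventional treatment to both arms, and nothing says that these drugs start at day 0. They lack the one-arm exposure on which this point rests.
- *Baseline and control samples are clean blanks, so anything unique to the JTTF arm at week 12 can be deleted.* Inclusion criterion 4 (section 2.4) restricts earlier Chinese medicine only in the experimental group, only for diabetes and NAFLD, and only for at least 2 weeks. Deletion could also discard an endogenous metabolite that appears because of treatment, which is the signal sought. Knowing which arm is JTTF would conflict with section 2.9, which keeps analysts and statisticians unaware of allocation.
- *The Fisher values measure the problem.* They show only that an assumed large difference in detection is significant.

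**Conclusion.** The point holds in a limited form. With samples only at baseline and at the end of JTTF dosing, and JTTF in one arm only, no comparison in section 2.8.5 can by itself tell JTTF-derived compounds from endogenous change. Such compounds may be selected, passed to targeted and pathway analysis, and read as mechanism. The number affected cannot be estimated from the documents.

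The conclusion rests on two things: that some JTTF-derived material is still detectable in a fasting sample at the end of treatment, which is plausible but not shown; and that no separating rule exists elsewhere, which the article alone cannot settle. The consequence is confined to the metabolomic objective and the mechanism claim. Visceral fat area, the TCM score and the clinical secondary outcomes are not touched. The change should be made, because it is inexpensive and has to be fixed before results are seen. Removing features afterwards would be discretionary.

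**What to change.** Add to section 2.8.5, to apply after the untargeted screen and before targeted and pathway analysis:

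1. Flag every feature that matches a JTTF constituent or a known biotransformation product of one, starting from the profile in the Introduction and Supplementary Material S1.
2. Report flagged features separately as exposure markers.
3. Base the targeted step, the pathway analysis and the mechanism claim on the remaining features.
4. Repeat the analysis without the filter as a sensitivity analysis.
5. Features seen only in the week-12 samples of one coded group may be sent for annotation review, but are not removed automatically. Coded groups keep the analysts blinded.

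**Cost.** This is analysis work only, with no new sample, visit, assay or change to treatment. The Introduction names five constituents and no biotransformation products, so the match list has to be extended from outside references before the data are examined. The small downside is that an endogenous metabolite that shares a signal with a herbal compound may be set aside. The unfiltered analysis would show it.
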